#### Economic evaluation

For the economic evaluation, all cost data will be inflated to AUD$ 2021/22 (final year of data collection) using the consumer price index (CPI) (http://www.abs.gov.au/ausstats), and will take a health-care sector perspective, with a rehabilitation admission and 30-day re-admission time horizon. Discount rates will not be applied due to the limited time horizon. Six months after the end of the 2022 financial year (i.e., December 2022), all data will be available from the costing unit of each participating health service.

The primary economic outcome is the *incremental cost-effectiveness ratio (ICER)*, comparing the intervention and control groups using the health service cost, including 30-day re-admissions, as the numerator, and the utility data (quality adjusted life years (QALYs)) or effectiveness data (FIM™) as the denominator. A secondary economic outcome is the *cost of implementation* which will be recorded to inform future adoption and scaling of My Therapy and to understand the cost of the My Therapy intervention, independent of the health service costs for each rehabilitation patient (details in data analysis section).

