#### Statistical analyses

Analyses will only include data from patients who were admitted and discharged during the ward’s control condition period or experimental condition period. Patients still admitted to the rehabilitation wards at the end point of the study will not be included. It is expected that due to the step-wedged design, this will equally exclude long-stayers in the control and experimental condition periods. Each analysis will use individual patient-level data, clustered within the ward, and will use the length of time (in weeks) of experimental exposure as an effect modifier [32]. Length of time of exposure to the experimental condition is an important consideration when an intervention may take time to settle into usual practice and where there may be a cumulative effect [32]. Analyses will be conducted on an intention-to-treat basis.

The analyses will compare the FIM™ and the health-related quality of life utility index score between the control and the intervention groups. Health-related quality of life scores from the EQ-5D-5L will be converted from raw scores to a utility index based on an Australian population [46, 47]. The proportion of people who achieve a MCID of 22 points in FIM™ [35, 37] will be analysed using mixed effects logistic regression, and the change in FIM™ score and utility index will be ana-lysed using mixed effects linear regression. Length of stay will also be analysed via a linear regression model.

While not powered for a secondary analysis, there will be an exploratory secondary analysis of the same outcome measures within each of the clusters and for the two home-based bed-substitution wards. Other secondary outcomes will be compared between groups using univariable analyses. All outcomes will be reported with 95% confidence intervals and analyses will assume a significance of *p* < 0.05.

For the economic evaluation, the primary outcome will be presented as cost-effectiveness and cost-utility analyses, reporting (i) the cost per MCID in FIM™ achieved; and (ii) the cost per QALY gained. Costs will include the rehabilitation length of stay, acute transfers within the rehabilitation stay and unplanned re-admissions within the 30 days post discharge. The QALYs will be calculated using the utility index scores.

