The mean cost difference will be determined between the two groups using a linear regression model [48]. Incremental cost-effectiveness ratios will be determined for both the FIM™ and utility index using the cost as the numerator, and the utility or effectiveness data as the denominator. All analyses will use individual patient-level data, will be clustered within the ward, and will use the length of time (in weeks) of experimental exposure as an effect modifier [32]. The ICERs for the cost per MCID achieved will be analysed using mixed effects logistic regression, and the ICERs for the cost per QALY gained will be analysed using mixed effects linear regression. Confidence intervals around the individual ICERs for utility and effectiveness will be calculated using the bootstrap method with 5,000 repetitions [49]. Individual ICERs will use the central limit theorem to generate the confidence ellipses, and the cost effectiveness acceptability curves (CEACs) [49] to inform the probability that My Therapy is less costly and more beneficial compared with usual care alone, with a $50,000 per QALY gained [50] threshold to determine cost-effectiveness.

A cost-analysis will be utilised to determine the cost of implementation. Data will be presented within two time periods; (i) the preparation period while under usual care conditions as well as the three months prior to commencing My Therapy (e.g., materials purchased and staff education sessions), and (ii) the implementation period while under experimental conditions (from commencement of My Therapy through to the end of the inpatient data collection indicating business as usual). Periods (i) and (ii) together will represent the full cost of My Therapy implementation (i.e., preparation, implementation and transition to business-as-usual conditions), whereas just period (ii) will represent the costs under business-as-usual conditions (i.e., just implementation and transition to business-as-usual conditions).

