As each ward will have a different time length for the preparation period and the implementation period, depending on their point of randomisation, costs will be presented per patient (total costs divided by the total number of patients who participate in My Therapy), and per ward (total costs divided by the total number of wards; n = 8) using independent *t*-tests (mean, standard deviation). Resource utilisation will be reported as real and in-kinds costs and these will include exercise materials purchased specifically for My Therapy (reported as market rate at the time of purchase); education for staff and patients, site coordinator time, marketing and communication, as well as therapist time to prescribe and progress My Therapy (staff costs based on EBA rates for Health Professionals) [51]. Costs will not include incidental nursing, medical or other staff time spent encouraging patient participation in My Therapy.

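### The ICER numerator leaves out any My Therapy cost not already in the hospital costing data, which tilts the primary economic outcome toward My Therapy

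*Protocol article*

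**What the plan says.** In the protocol article, Outcomes, Economic evaluation, the primary economic outcome is an ICER "comparing the intervention and control groups using the health service cost, including 30-day re-admissions, as the numerator". The evaluation "will take a health-care sector perspective", over the admission plus a 30-day re-admission window, with data from each participating health service's costing unit. Data Analysis, Statistical analyses, lists the components: "Costs will include the rehabilitation length of stay, acute transfers within the rehabilitation stay and unplanned re-admissions within the 30 days post discharge". That cost feeds the ICERs, the confidence ellipses, the acceptability curves and the comparison with $50,000 per QALY.

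The cost of My Therapy is handled elsewhere. Under Economic evaluation it is a secondary outcome, recorded for future adoption and "to understand the cost of the My Therapy intervention, independent of the health service costs for each rehabilitation patient". Under Statistical analyses, "A cost-analysis will be utilised to determine the cost of implementation". This separate analysis covers purchased exercise materials, education of staff and patients, site coordinator time, marketing, and "therapist time to prescribe and progress My Therapy (staff costs based on EBA rates for Health Professionals"). It has two periods: (i) preparation and (ii) implementation, "whereas just period (ii) will represent the costs under business-as-usual conditions". The per-patient figure divides total cost by the number of patients who take part in My Therapy.

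**The concern.** The comparison is My Therapy plus usual care against usual care. An incremental cost for that comparison has to contain what My Therapy itself consumes. The article assigns those resources to a different analysis and nowhere brings them back into the numerator. This is more than a detail left to an analysis plan: the article states the numerator's components and states where the intervention cost goes instead.

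At stake are the cost per MCID, the cost per QALY, the probability that My Therapy is both cheaper and better, and the verdict at $50,000 per QALY. Reporting the implementation cost alongside does not correct any of these. A reader could add a mean cost to the mean cost difference by hand, but could not rebuild the acceptability curve that way. The clinical primary outcome is not affected.

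**Working it through.** The article gives no cost, QALY or ICER figure, so there is nothing to reproduce. The direction of the error follows from algebra. Its size per dollar follows from one planned input, and the QALY side needs assumptions.

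**Inputs from the article**
- Planned proportions reaching the MCID: 22% and 10% (Sample size calculation), so dE = 0.22 − 0.10 = 0.12.
- Length of stay: 18.5 days (Sample size calculation).
- Post-discharge window: 30 days (Economic evaluation).
- Threshold: $50,000 per QALY (Statistical analyses).

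**Inputs not in the article (assumptions)**
- C, the My Therapy cost per experimental patient that the costing data do not capture; zero for control patients. Shown per $100.
- Utility gain at discharge: 0.02 to 0.10.
- Shape of the gain: linear over the stay and nothing after, or linear over the stay and then held for 30 days.

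**Direction**
- As planned: ICER = dC_health / dE.
- With the missing cost: ICER = (dC_health + C) / dE.
- Understatement when dE is positive: C / dE. Whatever the sign of dE, incremental net benefit is overstated by C per patient, so the acceptability curve moves the same way.

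**Cost per MCID**
- $100 / 0.12 = $833 for each $100 of C.
- If C were $100 to $300: $833 to $2,500 per MCID.

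**Cost per QALY**
- Stay only: dQALY = gain × (18.5/2)/365.25.
- Stay plus 30 days: dQALY = gain × (18.5/2 + 30)/365.25.
- The C whose value alone equals the QALY gain at the threshold is $50,000 × dQALY.

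| Assumed gain | Shape | dQALY | C equal to the QALY value | Shift per $100 of C |
|---|---|---|---|---|
| 0.02 | stay only | 0.00051 | $25 | $197,432 per QALY |
| 0.02 | stay + 30 days | 0.00215 | $107 | $46,529 per QALY |
| 0.05 | stay only | 0.00127 | $63 | $78,973 per QALY |
| 0.05 | stay + 30 days | 0.00537 | $269 | $18,611 per QALY |
| 0.10 | stay only | 0.00253 | $127 | $39,486 per QALY |
| 0.10 | stay + 30 days | 0.01075 | $537 | $9,306 per QALY |

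Because the horizon is short, the QALY difference is small under every row, and the cost per QALY is sensitive to modest amounts per patient. The table shows that sensitivity only. It leaves out any saving from a shorter stay, so it does not predict the result.

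**The case against.** The strongest reply is that much of the cost may already be counted. Under Usual care and intervention, My Therapy is delivered by the occupational therapists and physiotherapists whom the health service already employs, and the Background reports that the pilot needed no extra staff. Their time may sit inside the costed stay. The component list need not be exhaustive, and the statement that the implementation cost is independent of patient-level costs could describe how it is reported rather than an exclusion.

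Part of this stands. A reader might infer that the whole cost of My Therapy is omitted; the article does not show that, because the content of the costing-unit data is not described. But it does not say that therapist time is captured either. Nor does anything in the component list bring in purchased materials, education, coordinator time or marketing.

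A reader might also set an assumed $100 to $300 per patient against the $127 or $537 above and conclude that the omission consumes most of the benefit. The documents do not support that: both the cost and the utility gain are assumed, and the Background names a shorter stay as the reason My Therapy should be cost-effective, a saving that such a ratio ignores.

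Finally, a reader might say that the stated perspective is simply false and that care shifted out of hospital would look free. That goes too far. The restriction to the same health service is written only for the clinical re-admission outcome, the horizon is openly limited, and the two home-based wards are trial wards whose stays fall within the listed costs. What remains is narrower: costs come from participating services' costing units, and post-discharge rehabilitation is recorded as yes or no but is not in the cost list. The sector label therefore claims more than the listed costs show.

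**Conclusion.** The point holds for whatever part of My Therapy's cost the costing-unit data do not already contain. Followed as written, the plan leaves that part out of the incremental cost and biases the ICERs, the acceptability curve and the $50,000 per QALY decision toward My Therapy. The bias is C/dE: about $833 per MCID for each $100 per patient, if the planned difference of 0.12 is realised. The direction is certain for any positive C. The total size cannot be derived, because the documents give neither C nor a utility gain. Since this is the primary economic outcome, it should be settled before analysis.

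**What to change.** 1. State which My Therapy resources are already in the costing-unit data at each health service.
2. Before computing the ICERs and acceptability curves, add to each experimental-condition patient the per-patient My Therapy cost that is not already there. Count existing therapists' time only where it is not already costed. Exclude coordinator work done only for the research, such as the weekly record checks and the falls extraction.
3. Divide by all experimental-condition patients, not only those who took part, so that the cost matches the intention-to-treat comparison.
4. Base case: recurring period (ii) costs plus materials bought in period (i) but used by patients. Period (ii) alone would miss these, since the article gives purchased materials as an example of preparation cost. Scenario: the full cost of (i) and (ii), which also brings in the staff education of the preparation period.
5. Describe the perspective as that of the treating health service, unless re-admissions elsewhere and follow-up rehabilitation are costed.

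The cost is a change of wording and a little more analysis, because these costs are already to be collected; separating research from delivery time needs a coordinator time record. Costing care elsewhere would need further data, which the relabelling avoids. The ICER will be less favourable to My Therapy by the amount added.

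### Cost per MCID is assigned to a logistic model without the risk difference it needs, and the acceptability curve is described as a probability of dominance

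*Protocol article*

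**What the plan says.** The Economic evaluation section under Outcomes makes the ICER the primary economic outcome. The Statistical analyses section then sets out how it is obtained:

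- Numerator: "The mean cost difference will be determined between the two groups using a linear regression model".
- Ratio: ICERs are formed "using the cost as the numerator, and the utility or effectiveness data as the denominator".
- Models: "The ICERs for the cost per MCID achieved will be analysed using mixed effects logistic regression". The QALY ratio is assigned in the same way to a mixed linear model.
- Uncertainty: "Confidence intervals around the individual ICERs for utility and effectiveness will be calculated using the bootstrap method with 5,000 repetitions". Confidence ellipses based on the central limit theorem are also planned.
- Acceptability curves: these are "to inform the probability that My Therapy is less costly and more beneficial compared with usual care alone", and $50,000 per QALY gained is the "threshold to determine cost-effectiveness".

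All economic analyses are to be clustered by ward, with weeks of exposure as an effect modifier. The article does not say how the logistic fit becomes a difference in proportions, and it does not mention net benefit.

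**The concern.** Two statements do not match the quantity to be reported.

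First, an ICER is a ratio of two group-level differences, so it is not a patient outcome that a logistic model can take. Even if the model is meant only for the effect part, its treatment coefficient is a log odds ratio. Cost per additional MCID needs the extra proportion of patients who reach the MCID.

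Second, being cheaper and better at once is dominance, and its probability does not depend on any willingness-to-pay threshold. An acceptability curve does depend on the threshold. At $50,000 per QALY it gives the probability that net benefit is positive. That includes cases where the programme costs more but is worth it, and cases where it does slightly worse but saves enough. A health service told that the curve's value is the chance of saving money and improving outcomes could be badly misled.

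A narrower worry concerns the ICER interval. The Background hypothesises better outcomes and cost-effectiveness through shorter stays, which points towards savings with benefit. Ratios there are negative, and a negative ratio does not say which of the two differences is negative.

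**Working it through.** The article gives no economic figure to reproduce. The MCID rates below are the pilot rates in Sample size calculation. The article gives no cost differences, QALY differences or standard errors, so those used here are assumptions for illustration.

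**1. Scale of the MCID denominator**

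- Risk difference: 0.22 − 0.10 = 0.12.
- Odds ratio: (0.22/0.78) / (0.10/0.90) = 2.54; its logarithm is 0.93.
- Same odds ratio at a 5% control rate: odds 0.0526 × 2.54 = 0.134, proportion 0.118, risk difference 0.07.
- Same odds ratio at a 40% control rate: odds 0.667 × 2.54 = 1.69, proportion 0.629, risk difference 0.23.

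For an assumed cost difference of $1,000, cost per additional MCID would be about $14,700, $8,300 or $4,400 at control rates of 5%, 10% and 40%, all with the same odds ratio. The ratio is fixed only after predicted probabilities are averaged over patients. Because weeks of exposure modify the effect, they must also be averaged over exposure time.

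**2. Acceptability curve against dominance**

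Let C be the cost difference and Q the QALY difference, taken as normal and uncorrelated, with λ = $50,000.

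- P(net benefit > 0) = Φ[(λQ − C) / √(SE_C² + λ²SE_Q²)]
- P(dominance) = Φ(−C/SE_C) × Φ(Q/SE_Q)

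| C (SE) | Q (SE) | P(net benefit > 0) | P(dominance) |
|---|---|---|---|
| +1,000 (500) | 0.03 (0.006) | Φ(500/583) = 0.80 | 0.02 |
| +500 (500) | 0.02 (0.006) | Φ(500/583) = 0.80 | 0.16 |
| −500 (500) | 0.004 (0.004) | Φ(700/539) = 0.90 | 0.71 |
| −3,000 (1,000) | −0.01 (0.005) | Φ(2,500/1,031) = 0.99 | 0.02 |

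A simulation of 400,000 draws agrees (0.805 and 0.022 for the first row). With correlations of −0.3 and 0.3, the first row gives 0.78 and 0.84 against 0.02, and the third gives 0.88 against 0.73 and 0.93 against 0.69. Over all cases and correlations run, the gap is about 0.15 to 0.97.

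**3. Interval for the ICER**

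Simulated percentile intervals stand in for the bootstrap.

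- Effect well away from zero (assumed cost 1,500, SE 400; effect 0.12, SE 0.02): 5,705 to 22,293, against 5,706 to 22,280 by Fieller's method. The interval works.
- Effect near zero (assumed cost −500, SE 500; QALYs 0.004, SE 0.004): about −1.5 million to +1.3 million. About Φ(−1) = 0.16 of replicates have a negative denominator.
- Sign ambiguity: −1,000/0.02 and +1,000/(−0.02) are both −50,000.
- MCID denominator: the stated power of 0.99 at two-sided 0.05 implies effect/SE of about 1.96 + 2.33 = 4.29, so the chance of a negative replicate is about 0.00001 on the plan's own assumptions. The risk lies mainly with the QALY ratio.

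**The case against.** The strongest reply is that one loose sentence is being read against a sound paragraph. The section models the cost difference separately, defines the ratio correctly, and assigns logistic and linear models to the MCID and utility outcomes in the clinical analysis. The natural reading is that these models supply the effect component. Converting a logistic fit to a risk difference is routine analysis-plan detail, and that plan is not shown. This reply mostly stands as to intent. It does not cure the sentence, which names a model whose output is not the denominator and ties it to the ICER itself.

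On the acceptability curve, the reply is that the same sentence also names confidence ellipses, which can inform a dominance probability, and that the threshold shows the usual reading was intended. That shows both analyses were in view. The sentence still merges them and attaches only the dominance description.

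A reader might infer more than the article supports:

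- That none of the planned methods gives what is claimed. This is not so. Mixed linear regression gives the mean QALY difference directly, the cost model is appropriate, and a bootstrap ICER interval is standard where the effect is clearly non-zero.
- That cost will be divided by the log odds ratio, understating cost per MCID by 0.93/0.12, or 7.8-fold. The article proposes no such division.
- That an ICER interval loses its meaning whenever replicates cross any quadrant. If only cost changes sign while the effect stays positive, the ratio passes smoothly through zero.

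Making net benefit the main inference throughout would be partly a matter of preference.

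**Conclusion.** Two statements are wrong as written, and both bear on what the primary economic outcome reports. Logistic regression does not by itself yield cost per additional MCID: at the pilot rates it gives an odds ratio of 2.54 where 0.12 is needed, and the same odds ratio is compatible with risk differences from about 0.07 to 0.23 over control rates of 5% to 40%. The acceptability curve is not the probability of dominance, and in the illustrations the gap runs from about 0.15 to 0.97.

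The first result rests only on the pilot rates and arithmetic. The second holds by definition, but its size depends on assumed costs, QALYs, standard errors and correlations, so it shows what can happen rather than the error in this trial. The ICER interval is a conditional weakness, confined mainly to the QALY ratio. The primary clinical analysis is unaffected.

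**What to change.** - **Cost per MCID:** state that the denominator is the marginal (standardised) risk difference from the mixed logistic model, averaged over patients and exposure time, and that the ICER is the modelled cost difference divided by it.
- **Cost per QALY:** reword so that mixed linear regression estimates the mean QALY difference rather than the ICER.
- **Acceptability curve:** define it as P(net benefit > 0) at each threshold, including $50,000 per QALY.
- **Dominance:** report the probability of being both less costly and more effective separately, as the share of joint bootstrap replicates in that quadrant. Cost and effect must come from the same resample.
- **Interval:** keep the bootstrap ICER interval where the effect difference is clearly away from zero and the sign of the ratio is unambiguous. Where replicates cross zero effect, report incremental net benefit with a 95% CI and the cost-effectiveness plane instead.

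The cost is a few sentences in the analysis plan and modest programming. No new data are needed, and the design does not change.

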### Design

A stepped-wedge cluster randomised trial design will be conducted over 54 weeks, involving nine blocks of six-weeks duration (Fig. 1) [32]. Randomisation refers to the time when each ward crosses over from usual care to experimental conditions. Three months prior to trial commencement, a blinded researcher, not involved in the assessment or delivery of intervention, will randomise wards to the order of commencement of My Therapy using a computer-generated number sequence. Each ward will transition from the usual care condition (control group receiving usual care) to the experimental condition (intervention group receiving My Therapy in addition to usual care) sequentially at six-week intervals until all sites have crossed over to the experimental condition. Therapists and assessors will not be blind to group allocation and they will be informed of their upcoming cross over six weeks prior to cross over. This is due to the practical need to provide My Therapy education to the staff in the six weeks prior to commencing. In addition, patients will not be blind to group allocation due to the need to educate and engage patients in the My Therapy program.

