### Setting and participants

The project will take place within eight rehabilitation wards (totalling over 200 rehabilitation beds) across four Victorian health networks (see anzctr.org.au for study sites). At one health service, the two wards will incorporate home-based bed-substitution; all others will be located within inpatient facilities. We will include all patients aged 18 years or older undergoing rehabilitation on the selected rehabilitation wards during the trial period, of any rehabilitation diagnosis. Patients who do not speak English and those with a cognitive impairment will not be excluded. We will exclude any patients without coverage under Australia’s universal health care program (Medicare).

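### Cost of implementation: independent t-tests have no independent groups to compare, and dividing by eight wards does not adjust the period-specific cost for unequal period lengths

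*Protocol article*

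**What the plan says.** The protocol article, Economic evaluation (under Outcomes), makes the cost of implementation a secondary economic outcome, "which will be recorded to inform future adoption and scaling of My Therapy".

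The Statistical analyses section splits this cost into two periods. Period (i) is "the preparation period while under usual care conditions as well as the three months prior to commencing My Therapy". Period (ii) runs from the start of My Therapy on the ward to the end of inpatient data collection. The two together are to give the full cost of implementation. Period (ii) alone is to stand for cost under business-as-usual conditions.

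The section then gives its reason for the form of presentation: "As each ward will have a different time length for the preparation period and the implementation period". Costs will therefore be shown in two ways. The per-patient figure takes as its divisor "the total number of patients who participate in My Therapy". The second way of showing them is "per ward (total costs divided by the total number of wards; n = 8) using independent"; the method so named is the t-test, glossed in brackets as a mean and a standard deviation. The resources costed are those of My Therapy: materials bought for it, education, coordinator time, communication, and therapist time to prescribe and progress it.

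**The concern.** There are two separate difficulties.

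- **The test.** An independent-samples t-test needs two independent groups and a contrast. The text names neither. Usual care has no implementation cost to set against My Therapy, and the two periods are measured on the same wards.
- **The divisor.** The per-ward figure is introduced as a response to unequal period lengths, yet dividing by eight takes no account of weeks.

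The outcome is meant to guide services that may adopt the program. An adopting service that takes the period (ii) per-ward figure as a running cost would be reading the cost of an average number of trial weeks. It would also be reading an SD that reflects how long each ward happened to be in the period, and not how much wards differ in cost.

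**Working it through.** **Inputs**

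- Trial length (Design): "conducted over 54 weeks, involving nine blocks of six-weeks duration".
- Crossover (Design): wards cross "sequentially at six-week intervals until all sites have crossed over to the experimental condition".
- Wards (Setting and participants): "The project will take place within eight rehabilitation wards".
- Patient flow, for illustration (Sample size calculation): 340 patients per ward over 54 weeks.
- Assumption: one ward crosses at each step. Figure 1 is not available, but eight wards and nine blocks imply this.
- Assumption, for illustration: an identical weekly cost c in every ward.

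**Step 1. Reproduce the trial length.** 9 blocks × 6 weeks = 54 weeks, as stated.

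**Step 2. Weeks per ward.** The ward crossing after block k (k = 1 to 8) has 6k usual-care weeks and 6(9 − k) implementation weeks.

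| Crossover after block | 1 | 2 | 3 | 4 | 5 | 6 | 7 | 8 |
|---|---|---|---|---|---|---|---|---|
| Usual-care weeks | 6 | 12 | 18 | 24 | 30 | 36 | 42 | 48 |
| Implementation weeks | 48 | 42 | 36 | 30 | 24 | 18 | 12 | 6 |

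Each column sums to 54. Both rows come from the same eight wards, so a comparison of periods is matched within ward.

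**Step 3. Period (ii) cost per ward as planned.**

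- Total implementation time: 8 × 27 = 216 ward-weeks.
- Mean: 216c / 8 = 27c.
- SD of weeks: deviations from 27 are ±3, ±9, ±15 and ±21. Sum of squares = 2 × (9 + 81 + 225 + 441) = 1,512. SD = √(1,512 / 7) = 14.7 weeks.
- SD of cost: 14.7c, and 14.7 / 27 = 54% of the mean.

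At an assumed $500 per week, this is a mean of $13,500 and an SD of $7,348, although no ward costs more per week than another.

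**Step 4. The same data per ward-week.** 216c / 216 = c, with a between-ward SD of 0. At $500 per week the result is $500.

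**Step 5. The pooled per-patient figure.** Patients per ward-week = 340 / 54 = 6.30. Patients under implementation = 216 × 6.30 ≈ 1,360. At $500 per week, cost per patient = 500 × 216 / 1,360 ≈ $79. Because patients accrue with time, this divisor absorbs unequal length for costs that scale with patients.

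**Step 6. The total over both periods.** If the three months precede trial start, every ward spans 54 weeks plus three months. If they precede each ward's own crossover (taking three months as 13 weeks), the window reaches back before trial start by 13 − 6 = 7 weeks in the first ward and 13 − 12 = 1 week in the second. Spans are then 61, 55 and six times 54 weeks. On either reading the total is nearly or exactly balanced across wards.

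**The case against.** The strongest reply is that only a description was meant. The sentence speaks of presenting costs and puts mean and standard deviation in brackets after the test, so the t-test may be a misnomer. That is plausible. But the same section promises 95% confidence intervals and a 5% significance level for all outcomes, so a reader could take the test literally. The wording needs correcting on either reading.

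It can also be said that the protocol states no test of period (i) against period (ii), and that it plans exploratory looks at home-based wards, which are different wards from the inpatient ones. Both points are true. The protocol does not apply the home-based split to this outcome, so no independent groups are named for it.

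Several stronger readings are tempting but unsupported:

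- *The average per-ward cost depends on the random crossover order.* It does not. With equal weekly costs it is 27c whichever ward takes which step. What misleads is its SD and its use as a ward's running cost.
- *The t-test would give a standard error wrong by a known factor.* No contrast is stated, and the documents do not say how costs accrue. Preparation examples are materials and education, and staff education falls in the six weeks before crossover for every ward.
- *Per-patient cost is distorted by early wards having many more My Therapy patients than late ones.* The stated figure pools total cost over total patients. It is not an average of ward-level values.
- *Dividing by participants breaches intention-to-treat.* Cost per recipient is a legitimate descriptive figure.
- *The three months overlap usual-care time, so costs are counted twice.* Overlapping dates in a combined window do not mean that a cost is entered twice.

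**Conclusion.** The point stands as a correction to a secondary, mainly descriptive outcome. No independent-samples test applies to the implementation cost as defined. The period (ii) per-ward figure does not serve its stated purpose: it is the cost of 27 weeks on average, and at a constant weekly cost its between-ward SD is 54% of the mean purely because of the schedule.

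The size rests on one ward crossing per step and on a constant weekly cost. Real costs may be heavier just after crossover, which would change the 54% but would not put time into the divisor. The problem is confined to the period-specific per-ward figures and their SDs. Costs that scale with patients are handled by the pooled per-patient figure, and the primary outcome and the incremental cost-effectiveness ratios are analysed by other methods.

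**What to change.** In the cost-of-implementation paragraph of Statistical analyses:

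1. Delete the independent t-tests and describe the costs.
2. For period (ii), report cost per ward-week (total divided by 216 ward-weeks, or by the weeks actually delivered) alongside the pooled cost per patient.
3. For period (i), report preparation cost per ward.
4. Give the mean, SD and range over the eight wards for each.
5. If the two periods are compared at all, make the comparison paired within ward.

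This costs a change of wording and of denominators. The costs are already to be recorded, and ward-weeks follow from the schedule, so no new data are needed.
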